## Abstract

**Background:**

Injuries in or around the home are the most important cause of death among children aged 0-4 years old. It is also a major source of morbidity and loss of quality of life. In order to reduce the number of injuries, the Consumer Safety Institute introduced the use of Safety Information Leaflets in the Netherlands to provide safety education to parents of children aged 0-4 years. Despite current safety education, necessary safety behaviours are still not taken by a large number of parents, causing unnecessary risk of injury among young children. In an earlier study an E-health module with internet-based, tailored safety information was developed and applied. It concerns an advice for parents on safety behaviours in their homes regarding their child. The aim of this study is to evaluate the effect of this safety information combined with personal counselling on parents' child safety behaviours.

**Methods/Design:**

Parents who are eligible for the regular well-child visit with their child at child age 5-8 months are invited to participate in this study. Participating parents are randomized into one of two groups: 1) internet-based, tailored safety information combined with personal counselling (intervention group), or 2) personal counselling using the Safety Information Leaflets of the Consumer Safety Institute in the Netherlands for children aged 12 to 24 months (control group). All parents receive safety information on safety topics regarding the prevention of falling, poisoning, drowning and burning. Parents of the intervention group will access the internet-based, tailored safety information module when their child is approximately 10 months old. After completion of the assessment questions, the program compiles a tailored safety advice. The parents are asked to devise and inscribe a personal implementation intention. During the next well-child visit, the Child Health Clinic professional will discuss this tailored safety information and the implementation intention with the parents. The control group will receive usual care, i.e. the provision of Safety Information Leaflets during their well-child visit at the child's age of 11 months.

**Discussion:**

It is hypothesized that the intervention, internet-based, tailored safety information combined with personal counselling results in more parents' child safety behaviours.

**Trial registration:**

Current Controlled Trials NTR1836

## Background

Injuries in or around the home are the most important cause of death among children aged 0-4 years old. It is also a major source of morbidity and loss of quality of life [1-3]. In the Netherlands each year 30 children aged 0-4 years die caused by injuries in or around the home. Additionally 57.000 children aged 0-4 years are medically treated, of which 46.000 children at the emergency room of a hospital because of home injuries [4]. In order to reduce the number of injuries, the Consumer Safety Institute introduced the use of Safety Information Leaflets in the Netherlands to provide safety education to parents of children aged 0-4 years. These leaflets are well used in Child Health Clinics (CHC) and indications for a small effect on parental behaviours were gained through observational research [5,6]. However, despite current safety education, necessary safety behaviours are still not taken by a large number of parents, causing unnecessary risk of injury of young children. Improving the effectiveness of safety education to parents at CHC is therefore desirable. In an earlier study an E-health module with internet-based, tailored safety information was developed and applied. It concerns an internet-based, tailored information in combination with personal counselling for parents of infants on safety behaviours to be taken to the homes for their child [7-9]. In a process-evaluation it was found that majority of parents experience the new internet-based, tailored safety information as useful and applicable and that the CHC professionals are enthusiastic about the E-health module [8]. However there are no insights in the effects of the new internet-based, tailored safety information on parents' child safety behaviours compared to the current way of safety education.

### Objectives

The objective of this study is to evaluate the effect of online, internet-based, tailored safety information combined with personal counselling on parents' child safety behaviours. Additionally a process evaluation will be conducted to provide insight in the feasibility of the intervention. In this article the design of the study is described.

### Study hypothesis

The hypothesis of the study is that, after follow-up, parents of the intervention group show more safety behaviours regarding the prevention of falling, poisoning, drowning and burning compared to the control group. Furthermore we hypothesize that, determinants of safe behaviour, i.e. severity and self efficacy positively improve in the intervention group [10-14].

## Methods/design

### Study design

The study design is a randomized controlled trial (RCT), with a baseline measure point prior to the intervention and a follow-up measure point six months after the intervention. The course of the study with the specific items at each time point is described in table 1. Parents are individually randomized in an intervention group or a control group, according to a computerized random allocation generator. Parents had an equal probability of assignment to the groups. Parents of the intervention group receive internet-based, tailored safety information concerning the prevention of falling, poisoning, drowning and burning, combined with personal counselling at the CHC. Parents of the control group receive 'care as usual', personal counselling at the CHC using the Safety Information Leaflets (children 12-24 months old) of the Consumer Safety Institute in the Netherlands, concerning the same four safety topics.

**Table 1 T1:** Course BeSAFE study

Age of the child	Intervention-group	Control-group
**5-8 months**	▪ Informing parents about the study ▪ Request for participation (max. 2 reminders) ▪ Information letter ▪ Information folder ▪ Questionnaire	▪ Informing parents about the study ▪ Request for participation (max. 2 reminders) ▪ Information letter ▪ Information folder ▪ Questionnaire

**5-8 months**	▪ Parents log in on the website ▪ Parents provide informed consent ▪ Parents complete the **Baseline Questionnaire**	▪ Parents log in on the website ▪ Parents provide informed consent ▪ Parents complete the **Baseline Questionnaire**
		
	Randomization in intervention or control group	
		
**10 months**	Parents are invited through e-mail to complete the **online, internet-based, tailored safety information questionnaire **(max. 2 reminders)	

**11 months**	**Well-child visit** ▪ Personal counselling to discuss the **internet-based, tailored safety information and implementation-intention plan** ▪ Complete process-evaluation form by parents ▪ Complete process-evaluation form by Child Health Care professional	**Well-child visit** ▪ Usual Care: Safety Information Leaflets

**12 months**	Repeating the **internet-based, tailored safety information and implementation intention**, send to the parent by e-mail	

**17 months**	**Follow-up questionnaire** Follow up questionnaire send to the parent (max. 2 reminders)	**Follow-up questionnaire** Follow up questionnaire send to the parent (max. 2 reminders)

Data collection started in 2009 and will continue until 2011. This study is approved by the Medical Ethics Committee of Erasmus MC (MEC-2008-370).

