#### Youth Health Care organisations and Child Health Clinic teams

Managers of an opportunity sample of 26 Youth Health Care (YHC) organisations in the Netherlands were informed about the study and were contacted by the researchers to provide further information. Five YHC organisations in the provinces of Zuid-Holland, Noord-Brabant and Zeeland volunteered to participate in the study, with a total of 30 CHC teams. These teams cover both urban and rural regions in the Netherlands. Prior to the start of the study, the researchers arranged meetings to explain the procedure of the study and to instruct the participating CHC professionals.

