**Burns**		
- Thermostat-controlled tap	- Always	- Thermostat-controlled tap present
- Hot drinks	- Always	- Child never on parents womb when drinking hot drinks
- Kitchen	- Always	- Child never in the kitchen when cooking

The BeSAFE intervention consists of internet-based, tailored safety information combined with personal counselling at the CHC. The BeSAFE intervention module consists of a questionnaire assessing ten specific parents' child safety behaviours in the prevention of falling, poisoning, drowning and burning and determinants of safety behaviour (intentions, possible barriers and self efficacy); a library of safety messages; and algorithm to compose tailored health information for the parent [28]. Parents who give informed consent and fill in the baseline questionnaire receive an e-mail, when their child is about 10 months old, inviting them to participate in the BeSAFE intervention. As a first step parents complete a questionnaire, which is used to generate an online tailored safety advice. When parents have read their personal advice, they are invited to devise and inscribe an implementation intention. In this implementation intention parents plan specific actions for improving their safety behaviour and implementing them in their home situation at a specified time [29,30]. It consists of three parts, i.e. what, when and where. The safety information and implementation intention of each parent will be sent by e-mail to both the parent and the CHC professional, in order to prepare them for the well-child visit at 11 months. At the well-child visit the CHC professional will discuss the safety information and the implementation intention with the parent, using the techniques of motivational interviewing (MI). Motivational interviewing is believed to represent a brief and effective method for addressing behaviour change. Positive attitudes and experienced barriers of the parents are discussed in order to improve parents' child safety behaviours. One aspect of this motivational interviewing is giving attention to transforming positive intention into real behaviour [29-31]. CHC professionals were trained to apply motivational interviewing. Approximately four weeks after the well-child visit parents receive a reminder of their safety information and the implementation intention in order to strengthen the message.

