### Process-evaluation

In addition to the effect-evaluation a process-evaluation will be carried out. All parents who use the BeSAFE intervention module are asked to answer a few evaluating questions about the programme, i.e. which part of the advice parents have read, what there opinion is about the advice, do parents intend to change anything in there behaviour after reading the advice and what they think about the time they needed to complete the module. All parents in the intervention group and CHC professionals who provide the intervention will be asked to complete a process-evaluation form after the well-child visit at 11 months where the tailored safety information is discussed. It consists of questions regarding the feasibility of the intervention within the well-child visit, the perceived usefulness of the intervention and the discussed items during the well-child visit.

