## Discussion

This article describes the design of a randomised controlled trial regarding the BeSAFE intervention intended to promote parents' child safety behaviours. The study evaluates the effect of internet-based, tailored safety information combined with personal counselling on parents' child safety behaviours. We want to look at parents' child safety behaviours and want to compare these behaviours between the intervention and the control group. The new elements which are applied in the intervention group include a tailored safety advice for the parent, an implementation intention filled in by the parent and the discussion of this advice and implementation intention by the CHC professional with the parents using the techniques of motivational interviewing.

It is hypothesized that after 6 months of follow-up, parents in the intervention group show more child safety behaviour regarding the prevention of falling, poisoning, drowning and burning. Differences between subgroups (ethnicity and socio-economic status) regarding the effects of the intervention will be explored.

Strengths of the study are the power of the study, the randomized controlled design, and providing the intervention in daily practice of the CHC, which have a high attendance. The follow-up at 6 months allows investigating the effect of the intervention within an appropriate time schedule in the development of the child. Regarding the generalisability of the study results there can be noticed that it is a randomized controlled study conducted in the practice setting. The intervention is applicable in daily practice of the CHC professional, which will facilitate the implementation of the internet-based, tailored safety information if it is found effective. The data will be collected in both rural and urban areas of the Netherlands, resulting in higher generalisability.

Because the study relies on self-report by parents, misclassification might occur. Parents might give socially desirable answers by overstating their safety behaviours. A limitation of the study to be addressed includes the questionnaire and intervention being available in Dutch only. For this reason it is likely that only parents who master the Dutch language will participate in the study.

In conclusion, this study evaluates the effect of internet-based, tailored safety for parents of young children, combined with personal counselling at the Child Health Clinic.

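### Motivational interviewing training is not separated by arm and control visits are not recorded, so carry-over into the control arm could not be detected; the outcome models also name no CHC team term

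*Protocol article*

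**What the plan says.** Allocation is by parent: "Parents are individually randomized in an intervention group or a control group", and "Parents had an equal probability of assignment to the groups" (Study design). Parents come through five Youth Health Care organisations that "volunteered to participate in the study, with a total of 30 CHC teams". Before the start, "the researchers arranged meetings to explain the procedure of the study and to instruct the participating CHC professionals" (Youth Health Care organisations and Child Health Clinic teams). The Intervention section adds that "CHC professionals were trained to apply motivational interviewing". Neither statement divides staff by arm.

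The comparator is also a counselling visit: "Parents of the control group receive 'care as usual', personal counselling at the CHC using the Safety Information Leaflets" (Study design). It covers the same four topics and, in Table 1, takes place at the same 11-month visit. The Discussion lists among the new elements of the intervention arm the "discussion of this advice and implementation intention by the CHC professional with the parents using the techniques of motivational interviewing".

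On what is recorded at that visit, Process-evaluation (under Measurements) says: "All parents in the intervention group and CHC professionals who provide the intervention will be asked to complete a process-evaluation form". The form covers feasibility, perceived usefulness and items discussed. Table 1 shows the forms in the intervention column only; the control entry for the visit is usual care with the leaflets. The later Process-evaluation paragraph, under Statistical analyses, assesses adherence to BeSAFE elements only.

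The Effect-evaluation section specifies regression of the sum score on group, adjusted for baseline values, and logistic regression for dichotomous outcomes. CHC team is not mentioned. The limitations in the Discussion are self-report and Dutch-only materials.

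**The concern.** One component under test is a skill given to professionals, while allocation is by parent. A professional trained in motivational interviewing who also sees control parents may use it with them. That would move the control arm towards the intervention arm and shrink the difference. Because content is recorded in one arm only, the trial would have no data on whether this happened. A null result could then mean an ineffective programme or a diluted contrast. What was said in a visit cannot be reliably reconstructed afterwards.

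A second, smaller matter is that counselling is delivered through 30 teams but the stated models treat parents as independent. Whether that affects the standard error depends on whether teams differ in outcome level or in the size of the effect.

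**Working it through.** **Inputs from Power of the study:** difference 0.34, SD 1.7, alpha 0.05 (two-sided assumed), power 0.80, 30% loss, 420 completers per arm. **Teams:** 30. **Not in the documents, so assumed:** carry-over share c, baseline-to-follow-up correlation r, between-team variances.

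**The plan's own figure.** n per arm = 2 × (1.96 + 0.8416)² × 1.7² / 0.34² = 393, so 786 completers, or 786 / 0.7 = 1123 randomised. The plan has 840 and 1200, somewhat more than needed. With 420 per arm:
- SE = 1.7 × √(2/420) = 0.117.
- Power for 0.34 = Φ(0.34/0.1173 − 1.96) = 82.6%.
- Difference detectable with 80% power = 2.80 × 0.1173 = 0.329. Carry-over of about 3% (1 − 0.329/0.34) uses up the margin on this unadjusted basis.

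**Effect of carry-over.** The difference becomes 0.34 × (1 − c). The planned model adjusts for baseline. If 1.7 is the unadjusted SD and r = 0.5, the SE becomes 0.1173 × √(1 − 0.25) = 0.102. Power = Φ(difference/SE − 1.96):

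| c (assumed) | Difference | Power, unadjusted | Power, adjusted, r = 0.5 (assumed) |
|---|---|---|---|
| 0 | 0.340 | 83% | 92% |
| 10% | 0.306 | 74% | 85% |
| 20% | 0.272 | 64% | 76% |
| 30% | 0.238 | 53% | 65% |

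For the stair gate outcome (30% against 21% unsafe), moving the control rate towards the intervention rate by the same shares takes power from 85% to 77%, 68% and 57%. For storage of cleaning products (20% against 12%), it goes from 89% to 82%, 73% and 63%.

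**Leaving team out of the model.**
- *Team effects common to both arms.* With arms balanced within teams, the true SE is the naive SE × √(1 − ICC). The real type I error is then 0.049 at ICC 0.01 and 0.044 at ICC 0.05, which is slightly conservative.
- *Effect varies between teams.* With between-team effect variance τ², the variance of the difference is 2s²/420 + τ²/30.
  - τ² = 0.02s²: (0.02/30)/(2/420) = 0.14; √1.14 = 1.068. The naive SE is 1 − 1/1.068 = 6% too small and the true alpha is 6.6%.
  - τ² = 0.05s²: (0.05/30)/(2/420) = 0.35; √1.35 = 1.162. The naive SE is 1 − 1/1.162 = 14% too small and the true alpha is 9.2%.

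**The case against.** Several objections carry weight.

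- **Shared staff is an inference.** A reader might conclude that the same trained professionals certainly see both arms. The article does not say so, nor how many professionals were trained. Individual randomisation across 30 teams with no control staff described makes it likely, but a condensed article's silence does not prove it.
- **Most of the programme has no described route to controls.** A reader might infer that the whole intervention can leak. The module is opened by e-mail invitation, the implementation intention is written after the tailored advice, and the advice, plan and 12-month repeat are e-mailed. Table 1 gives controls none of these. The interviewing is described as a way to discuss that advice and plan, which controls do not have. Only general counselling style and informal action planning could travel, so the upper end of the 10–30% range would need counselling to account for a substantial part of the effect.
- **The unadjusted power figures are pessimistic.** The planned model adjusts for baseline, hence the second power column.
- **The team term could sit in an analysis plan that is not shown.** A reader might infer that the stated tests are invalid without it. They are not: common team effects make them slightly conservative. The alphas of 6.6% and 9.2% need an effect that varies between teams yet averages zero; if the programme has no effect in any team, there is no inflation. They also assume inference to a wider population of teams, whereas the organisations volunteered from an opportunity sample.

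What remains is that the plan fixes the visit record to one arm, so the amount of carry-over, large or small, would be unknown.

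**Conclusion.** The point holds in limited form. The trained counselling may reach control visits, the plan records visit content in the intervention arm only, and carry-over is not named as a limitation. A null result would therefore be ambiguous. At the assumed shares of 10%, 20% and 30%, the loss is about 8, 19 and 30 percentage points of power unadjusted (from 82.6%), and about 6, 15 and 27 points with adjustment at r = 0.5 (from 92%). The documents give neither a carry-over rate nor a correlation, so these figures show sensitivity and are not predictions.

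The missing team term is secondary. It understates the standard error, by about 6% or 14%, only if the effect variance between teams is 2% or 5% of the outcome variance, which is assumed.

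A reader might also infer that parents should have been randomised by team. The documents do not support that: individual randomisation is a sound choice here, and the weakness lies in what is measured around it.

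**What to change.** 1. **Record control visits.** For the remaining 11-month control visits, collect a short version of the items-discussed part of the form from parents or professionals. Word it neutrally, because asking directly about motivational interviewing or action plans could prompt their use. Report counselling content by arm beside the primary result, and state carry-over as a limitation. Cost: the form must be adapted, since feasibility and usefulness questions do not apply to controls, and there is a small burden on clinics. Collection began in 2009 and runs to 2011, so earlier control visits stay unrecorded.
2. **Add CHC team to the outcome models in Effect-evaluation.** Use a random team intercept for the sum score, and GEE or team-robust standard errors for the logistic models. Fit a team-by-arm slope as a sensitivity analysis only. Cost: a line in the analysis text and the team identifier in the data set.
3. **Keep individual randomisation.**

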### Study procedure and participants

Parents who are eligible for the regular well-child visit with their child at child age 7.5 months receive written information about the study and are invited to provide informed consent to participate in the study. All parents receive a singular, personal code to log in at the website of the study (www.besafe-onderzoek.nl). In 2009, 90% of all households in the Netherlands had access to the internet [15]. At the study website parents can find more information about the study and they can complete the questionnaires.

#### Youth Health Care organisations and Child Health Clinic teams

Managers of an opportunity sample of 26 Youth Health Care (YHC) organisations in the Netherlands were informed about the study and were contacted by the researchers to provide further information. Five YHC organisations in the provinces of Zuid-Holland, Noord-Brabant and Zeeland volunteered to participate in the study, with a total of 30 CHC teams. These teams cover both urban and rural regions in the Netherlands. Prior to the start of the study, the researchers arranged meetings to explain the procedure of the study and to instruct the participating CHC professionals.

